## Study design and population

The DetECT project has a prospective and exploratory design. Recruitment is planned to last 3 years. The study is conducted exclusively in adult (≥ 18 years) and legally competent severely depressed in-patients receiving treatment at the MPIP’s research clinic in the form of ECT. The study design is purely observational. Therefore, both the diagnostic and treatment process including the mode of ECT administration as well as pharmacotherapy is determined solely by the attending psychiatrist in joint decision with the patient based on the overall clinical situation in accordance with the German depression treatment guidelines [21]. Diagnosis is made by a trained psychiatrist in compliance with the depression criteria of the International Classification of Diseases 10th revision (ICD-10). Patients included in the study suffer from TRD that is defined in accordance with the FDA and EMA guidelines, i.e., two or more failed antidepressant treatments in adequate dosing and duration. Depression severity is evaluated via standardized self- and clinician ratings, as described later in detail. Inclusion and exclusion criteria are listed in Table 1.

**Table 1 Tab1:** DetECT eligibility criteria

Inclusion criteria
Age ≥ 18 years, legally competent, and desire to participate
Diagnosis of a depressive episode according to the ICD-10
Severity is confirmed using self- and foreign-rating psychometry
Treatment resistance (i.e. ≥ 2 failed antidepressant treatments)
Clinical indication and upcoming electroconvulsive therapy
Signed electroconvulsive therapy informed consent form
Signed informed consent documents for the DetECT study
Signed consent and participation in MPIP’s biobanking project
Proficient German language and communication skills
Exclusion Criteria
Age < 18 years (minor) or no desire to participate
Legal supervision or acute legal incompetence
Pregnancy and/or breastfeeding
Pervasive developmental disorders and/or intellectual disability
Acute substance abuse (e.g., alcohol, prescription, or illicit drugs)
Severe neurological disease (e.g., severe organic brain damage)
Acute or serious general illness (e.g., relevant anemia requiring transfusion)

In study participants, serial venous blood draws (prior fasting: ≥ 6 h) are performed before and after the first and seventh as well as after the twelfth ECT session. A detailed schematic of the study design is given in Fig. 1. Pre-ECT blood draws with a total volume of 36 ml include collection of ethylenediamine tetra acetic acid (EDTA) (Sarstedt, S-Monovette® K3 EDTA) and serum (Sarstedt, S-Monovette® Serum Gel) tubes as well as PaxGene Blood RNA Tubes (Qiagen) for the extraction and analysis of DNA and epigenetic measures (e.g., methylation patterns), RNA including messenger and micro-RNA (mRNA and miRNA, respectively), neuron-derived exosomes, purines, hormones, proteins, electrolytes, metabolic parameters, inflammatory markers, and peripheral blood mononuclear cells (PBMCs). Post-ECT blood draws include only EDTA and serum tubes (Sarstedt) for total of 10 ml. In a subset of *n* = 10 participants, which are recruited at the very beginning of the study’s field phase (DetECT pilot phase), the ECT blood collection after the first ECT consists of three time points (1 h, 3 h, and 6 h post). The rationale for this schedule is to characterize the temporal post-ECT dynamics. This would also allow to discriminate between an immediate ECT-induced release of brain-derived molecules and cells through the blood–brain barrier (fast pathway) or a delayed release via cerebrospinal fluid drainage (slow pathway). To achieve this, the pilot phase materials and data are analyzed with regards to the different multiomics read-outs to determine the optimal post-ECT time point for the study main phase. To reduce batch effects, samples are stored in the MPIP’s biobanking unit in freezers for later analyses with larger sample sizes.

In addition to the serial blood draws, participants are asked to answer the following self-rating questionnaires concerning their depressive and somatic symptoms on a weekly basis: Patient Health Questionnaires 9 and 15 (PHQ-9/-15) [122–125], the Questionnaire on Mental Capacity (FLei) [126], and the Beck Depression Inventory (BDI-II) [127–129]. The reference-interval of the self-rating questionnaires was customized from two (PHQ-9, BDI-II) and four (PHQ-15) weeks as well as six month (FLei) to the week prior to match the DetECT study design. Moreover, three clinician-rating instruments are assessed via a clinical interview in week 1, 4, and 7 of the study period: the Montgomery-Åsberg Depression Rating Scale (MADRS) [130, 131], the Hamilton Rating Scale for Depression with 21 items (HAM-D21) [132–134], and the DSM-IV derived Global Assessment of Functioning (GAF) [135, 136]. In addition to study related procedures, metabolic parameters (i.e., body mass index (BMI) or blood pressure (BP)) as well as medical information (e.g., patient and family anamnesis, past and recent medication including concomitant psychopharmacological treatment pre and during ECT allergies, drug use, psychiatric and somatic diagnoses) and sociodemographic data are extracted from patient records. See Fig. 1 for further detail.

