## Study timeline

The study period can be divided into four distinct consecutive work phases (see Fig. 2). Phase one commenced in September 2022 and will recruit minimum of the n = 10 pilot participants. It is estimated to last half a year. After completion, pilot materials and data are analyzed (Phase two). Here, measurements of highly dynamic parameters (e.g., RNA expression, neuron-derived exosome analyses, and immunological measures including cytokines and purines) are carried out and validated methodically. We expect this to yield meaningful and novel information about the post-ECT temporal dynamics of different biological read-outs. The focus of the laboratory and statistical analyses is at which time (i.e., either after 1 h, 3 h, or 6 h) potential biomarkers show the largest deflection from baseline. The timeframe for these analyses is expected to be half a year. Based on the biomarker dynamics of the pilot samples, the post-ECT blood collection interval for the DetECT main phase (Phase three) will be determined. In the main phase of the study, a total of *n* = 124 participants will be recruited over the course of 2 years. Finally (Phase four), the data obtained are analyzed and published. Here, the focus is not only on the creation of new scientific knowledge, but the clinical implementation of the identified biomarkers.

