### mRNA sequencing

Following mRNA extraction from thawed EDTA blood stored in PaxGene Blood RNA Tubes (Qiagen), we will use commercially available Library Prep Kits to generate sequencing libraries. Libraries will be multiplexed and sequenced on an Illumina® platform.

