## Prospective statistical analysis

The statistical analysis of the DetECT study mainly focuses on comparing ECT responders with non-responders (internal control group) within the sample. Clinical response indicated by overall and sub-domain changes in psychometry will serve as main dependent variables and analyses focus on within-subject changes over time. On the one hand, we aim to use variance and correlation analyses (e.g., repeated-measures ANOVA, Pearson’s r and correlation matrices), regression models (e.g., linear or logistic regression), and principal component analysis to first identify both significant main and interaction effects between biobehavioral parameters and treatment response. These analyses will be performed for all measures pre-, during, and post-treatment. Aside from using single parameters and the area under the curve as independent variables, we will employ index and score approaches (e.g., inflammatory indexing and Z scores) to allow combined analyses of functionally connected processes. Following these steps, we plan to employ linear mixed models (LMM) to examine if a single or parameter cluster is linked to remission, treatment response, failure, and side effects. As described above, we will also use single and combined as well as over time parameters, indices, or scores to perform LMM. Factors like the SES, comorbidities, smoking, concomitant pharmacological treatment (both general and psychiatry specific), and mode of ECT application (e.g., right-unilateral vs. left-anterior-right-temporal) will be used as covariates. Multiple comparisons correction will be applied. To further ensure that the identified associations are not only statistically significant, but also represent a relevant underlying biological mechanism, we will report both significance (p value) as well as effect size (e.g., Cohen’s d or comparable measures) in prospective DetECT publications, as recommended for instance by Goodman et al. 2019 [161].

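### The pilot is to use RNA expression at 1, 3 and 6 h to set the post-ECT draw time, but the post-ECT draws contain no tube for blood mRNA

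*Protocol article*

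**What the plan says.** Three sections of the protocol article bear on this.

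- **Study design and population** gives the content of the draws. Pre-ECT draws total 36 ml and hold EDTA and serum tubes "as well as PaxGene Blood RNA Tubes (Qiagen) for the extraction and analysis of DNA and epigenetic measures" and for RNA and a list of other analytes. The following sentence reads: "Post-ECT blood draws include only EDTA and serum tubes (Sarstedt) for total of 10 ml". The section then turns to the first 10 participants, for whom "the ECT blood collection after the first ECT consists of three time points (1 h, 3 h, and 6 h post"), and makes no exception to the tube rule for them.
- **mRNA sequencing** gives the laboratory route: "Following mRNA extraction from thawed EDTA blood stored in PaxGene Blood RNA Tubes (Qiagen"), libraries are prepared and sequenced. No other source of blood mRNA is described.
- **Study timeline** says that after the pilot "measurements of highly dynamic parameters (e.g., RNA expression, neuron-derived exosome analyses, and immunological measures including cytokines and purines) are carried out". The question put to these data is "at which time (i.e., either after 1 h, 3 h, or 6 h) potential biomarkers show the largest deflection from baseline", and the answer sets the post-ECT interval for the 124 main-phase participants. The caption of Fig. 2 again names RNA expression among the pilot measurements.

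**The concern.** The pilot exists largely to choose a sampling time. One of the read-outs named for that choice has no sample at any of the three candidate times if the tube list is followed. The interval would then be set without a read-out that the plan says informs it, and a main-phase draw time might be taken as suitable for RNA when RNA was never examined.

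Change in gene expression and regulation is also the first component of the primary hypothesis (Study hypotheses and objectives). If the investigators want the acute part of that change, the tube set has to provide for it when the blood is drawn. Blood not collected by the required route cannot be made good later from the freezer.

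**Working it through.** There is no stated figure to reproduce. The check sets each draw against the tube set assigned to it and the only mRNA route described.

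**Inputs**
- Pre-ECT tubes: EDTA, serum, PaxGene, 36 ml (Study design and population).
- Post-ECT tubes: EDTA and serum, 10 ml (same section).
- mRNA source: blood in PaxGene tubes (mRNA sequencing).
- Exosomal miRNA source: EDTA plasma (Neuron-derived exosomes and cargo analysis).
- Purine source: 40 µl of whole blood, measured at once (Purine measurements).

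**Blood mRNA by draw, as written**

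| Draw | Tube set | PaxGene? | Blood mRNA? |
|---|---|---|---|
| Before session 1 | pre-ECT | yes | yes |
| Pilot, 1 h after session 1 | post-ECT | no | no |
| Pilot, 3 h after session 1 | post-ECT | no | no |
| Pilot, 6 h after session 1 | post-ECT | no | no |
| Main phase, after session 1 | post-ECT | no | no |
| Before session 7 | pre-ECT | yes | yes |
| Main phase, after session 7 | post-ECT | no | no |
| Within 1 week after session 12 | not assigned | unclear | unclear |

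**Results**
- Pilot time points that can supply blood mRNA for the interval decision: 0 of 3.
- Main-phase draws taken directly after a session that can supply it: 0 of 2.
- Pre-ECT draws that can supply it: 2 of 2, so change from before session 1 to before session 7 can be estimated.

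**Could RNA expression mean something the post-ECT tubes can supply?**
- *Exosomal miRNA.* This comes from EDTA plasma and is available after ECT. But the Study timeline lists exosome analyses as a separate item beside RNA expression, so the two are not the same read-out.
- *EDTA blood moved into PaxGene tubes.* The phrase in the mRNA section could be read this way. But the tube list treats PaxGene as a tube of its own, present before ECT and excluded after it. If a transfer is meant, the text does not say that it is done after ECT.

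Neither reading reconciles the three sections.

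**The case against.** The strongest reply is that this affects one read-out in an exploratory pilot of 10. The list of dynamic parameters is given as examples. The stated rationale for the three time points is to tell fast from slow release of brain-derived material, and exosomes, cytokines and purines can all be measured from the post-ECT draws. This stands: the pilot can still choose a time. It does not remove the conflict, because RNA expression is named explicitly, in the text and in a caption.

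A second reply is that the article is condensed, Fig. 1 is not shown, and tube lists per draw may sit in a fuller document. That would explain missing detail. It does not explain an exclusive statement about post-ECT tubes that disagrees with other sections of the same article.

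Three stronger readings are tempting, and the document does not support them.

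- *That mRNA was planned at all five main-phase draws and most are lost.* No section plans this. Giving the larger set to pre-ECT draws and the smaller to post-ECT draws is a stated choice. The contradiction lies in the pilot.
- *That the analysis section demands post-session RNA.* It says "These analyses will be performed for all measures pre-, during, and post-treatment". This refers to phases of the treatment course, not to hours after a session. The pre-session 1, pre-session 7 and final draws would satisfy it.
- *That there is no end-of-treatment mRNA.* The draw within 1 week after session 12 is listed apart from the before-and-after pairs, and its tube set is not assigned. That is an ambiguity to settle, not a demonstrated loss.

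Nor does the primary hypothesis fail: it sets no acute time frame, and the change between the two pre-ECT draws addresses it.

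**Conclusion.** The conflict is real and lies within the article. With the tubes and the mRNA method as described, blood mRNA is available at none of the three pilot post-ECT time points. It cannot contribute to the choice of interval, which would rest on exosomal miRNA, cytokines and purines alone. For the same reason, no acute post-session mRNA response can be measured in the main phase.

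The damage stops there. The other dynamic read-outs and the longer-term mRNA change between the pre-ECT draws are unaffected.

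The conclusion assumes that the post-ECT tube sentence applies to the pilot draws, since no exception is given, and that the PaxGene route is the only one intended for blood mRNA.

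**What to change.** Reconcile Study design and population, Study timeline (with the Fig. 2 caption) and mRNA sequencing in one of two ways.

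1. **Collect the sample.** Add a PaxGene tube to the post-ECT set for the 1, 3 and 6 h pilot draws. Add it to the main-phase post-ECT draws as well if acute mRNA is wanted. The cost is a small extra volume and one tube at venepunctures already planned. At one tube per draw (an assumption; the article gives no number), this is 10 × 3 = 30 tubes in the pilot and up to 124 × 2 = 248 in the main phase.
2. **Narrow the aim.** If the pilot draws are already complete or volume prevents the extra tube, remove RNA expression from the read-outs that set the interval, and limit mRNA analyses to the draws that include PaxGene. The article says that the pilot began in September 2022 and was expected to last half a year, but not whether its draws are finished, so this may be the only route left for the pilot. It costs a few sentences and gives up the acute mRNA question.

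In either case, state which tube set is used at the draw within 1 week after session 12, so that end-of-treatment mRNA is secured. If EDTA blood is in fact transferred to PaxGene tubes after ECT, say so in the tube description.

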## Screening and recruitment

All patients who receive inpatient psychiatric treatment including a pending ECT for a confirmed TRD are informed about the DetECT study and the possibility of participating. This is done by the treating/responsible psychiatrist or another treatment team member. Rarely, first contact with the study team is made through an interested patient directly. If patients express an interest in participating, after receiving first and general information about the DetECT study, their eligibility and contact information is passed onto the MPIP Study Center. Study participation is completely voluntary. After obtaining the signed informed consent form, all study-related procedures are commenced.

## Study timeline

The study period can be divided into four distinct consecutive work phases (see Fig. 2). Phase one commenced in September 2022 and will recruit minimum of the n = 10 pilot participants. It is estimated to last half a year. After completion, pilot materials and data are analyzed (Phase two). Here, measurements of highly dynamic parameters (e.g., RNA expression, neuron-derived exosome analyses, and immunological measures including cytokines and purines) are carried out and validated methodically. We expect this to yield meaningful and novel information about the post-ECT temporal dynamics of different biological read-outs. The focus of the laboratory and statistical analyses is at which time (i.e., either after 1 h, 3 h, or 6 h) potential biomarkers show the largest deflection from baseline. The timeframe for these analyses is expected to be half a year. Based on the biomarker dynamics of the pilot samples, the post-ECT blood collection interval for the DetECT main phase (Phase three) will be determined. In the main phase of the study, a total of *n* = 124 participants will be recruited over the course of 2 years. Finally (Phase four), the data obtained are analyzed and published. Here, the focus is not only on the creation of new scientific knowledge, but the clinical implementation of the identified biomarkers.

**Fig. 2 Fig2:**
[figure not shown]
Schematic DetECT study timeline. The study period can be divided in four phases: (I) recruitment of the *n* = 10 pilot participants; (II) analyses of pilot materials and data. Primarily highly dynamic parameters (e.g., RNA expression, neuron-derived exosomes, immune cells, cytokines, and purines) are measured and validated. (III) Study main phase aiming to recruit a total of *n* = 124 participants over the course of 2 years. (IV) Finally, data are analyzed and published with a focus on the potential of the novel insights and biomarkers for clinical application (created with www.Biorender.com)

## Longitudinal psychometric measures

To simultaneously measure depressive, neurocognitive, and somatic symptoms longitudinally in DetECT participants, we have selected four self-rating and three clinician-rating instruments. Since DetECT patients suffer from severe TRD and are thus heavily affected, psychometry was tailored to minimize participant efforts, while maximizing read-outs and item validation options post hoc. Only German questionnaire versions were used (see [126, 131, 137–140]).

Self-rating questionnaires: The PHQ-9 and PHQ-15 are both subscales of the patient health questionnaire (PHQ), which have proven effective for monitoring depression and somatic symptom burden [141]. The PHQ-9 is a self-administered depression screening, which contains a dimensional answer category (0 = not at all; 3 = nearly every day) for the nine depression criteria derived of the DSM-IV [123, 142]. The BDI-II is, similar to the PHQ-9, a multiple-choice self-report questionnaire with high validity and reliability [127–129, 143]. It is composed of 21 items, which have values of 0 to 3, to assess the presence as well as severity of depression [127]. The PHQ-15, on the other hand, is a self-rating questionnaire to assess somatic symptom load via 15 questions (0 = not bothered at all; 2 = bothered a lot). Summary scores are used as indicators of somatic symptom burden [125]. The FLei is a comparatively novel measure of neurocognitive function. By use of 35 questions with answers ranging from 0 = never to 4 = very frequently, the following domains are assessed: (I) attention, (II) memory, (III) executive functions, (IV) control scale [126]. Based on the FLei domain and sum scores, a longitudinal neurocognitive profile can be computed.

Clinician-rating questionnaires: Both, the MADRS and HAM-D21 are obtained by trained study personnel in a clinical interview. The MADRS (10-question instrument) and the HAM-D21 (21 items) both assess depression presence and severity [130–134]. The GAF is a functionality and severity score for psychiatric disorders ranging from 0 (= maximum symptom severity and load, extreme sociofunctional impairment) to 100 (= no symptoms or impairment). The index accounts for overall psychiatric symptom severity and sociofunctional impairment [135, 136].

## Sample analytics: blood-based multiomics and biomarker screening

Using the collected and frozen within-subject blood samples, we aim to perform multiomics and deep phenotyping. To reduce batch effects and overall experimental variability, all laboratory measurements for a certain measure are performed together.

### Genotyping and epigenetic analyses

Using DNA isolated with a conventional extraction kit from EDTA blood, genotyping and epigenetic profiling will be performed using array-based approaches. Quality is ensured due to our in-house standard operating procedure.

### mRNA sequencing

Following mRNA extraction from thawed EDTA blood stored in PaxGene Blood RNA Tubes (Qiagen), we will use commercially available Library Prep Kits to generate sequencing libraries. Libraries will be multiplexed and sequenced on an Illumina® platform.

### Neuron-derived exosomes and cargo analysis

Neuronal exosome isolation will be performed based on the protocol by Saeedi and Nagy et al. 2021 [144]. In brief, exosomes extracted from EDTA-plasma will be enriched using neuronal markers (e.g., synaptosomal-associated protein of 25 kDa, SNAP-25). Subsequently, exosome cargo will be analyzed focusing on miRNAs.

### Cytokine and immune metabolite quantification

For cytokine quantifications, we plan to use custom-designed high-sensitivity immunomagnetic assays. Cytokine panels will be designed to reflect both pro- and anti-inflammatory states, in parts based on findings from large meta-analyses on cytokine changes in MDD [145]. Additionally, we will conduct ELISAs targeting other immunogenic metabolites like kynurenine and quinolinic acid [146].

### Purine measurements

Total purine levels (mM) are measured immediately after venous blood collection in 40 µl of whole blood using high-sensitivity electrochemical sensors (Zimmerman & Peacock). Serum uric acid levels from routine blood draws at admission and comorbid gout and/or anti-gout medication is extracted from patient records and used as a covariable.

